### Education control Group (EG)

This group will receive a book [76] published by PLE^2^NO’s scientific team. This book contains descriptions and tips for managing KOA in addition to educational and exercise information presented as images. Additionally, the participants will attend three monthly educational sessions that are one hour in length each regarding joint protection strategies, exercise, and self-management techniques. These sessions will be delivered by the coordinator of the PLE^2^NO project, who is a PhD Professor in the Faculty of Human Kinetics, and an Exercise and Health master’s student from the same institution. Telephone contacts will be established 15 days after each educational session to avoid withdrawals and to maintain closer monitoring.

### Assessments and procedures

The assessments will be performed one week prior to the start of the program (baseline), during the week following the final intervention (three months later), and at a 6-month follow-up, and will be done by PLE^2^NO team member(s) (all of whom are master students in exercise and health specialties) who are blinded to group allocation. Each evaluator performs the same test to avoid inter-rater variability. The assessments will be performed on the same day. To avoid overloading the participants, the physical tests and questionnaires will be performed alternately. Additionally, the physical tests involving load-bearing activities will be alternated with those that are performed while seated. The order of those tests and questionnaires were determined previously, in accordance with the statements already mentioned.

The main outcome will be self-reported pain (sub-score of the Knee Injury and Osteoarthritis Outcome Score –KOOS). The secondary outcomes will be: other KOA symptoms, KOA-specific health-related quality of life, self-efficacy, self-management behaviors, a healthier quality of life, a physically active lifestyle, coping strategies, aerobic capacity, functional strength, mobility, flexibility, gait speed, static balance and handgrip. All outcomes and instruments are illustrated in Table 2 and will be assessed at baseline, post-intervention and a 6-month follow-up.

**Table 2 Tab2:** Outcomes and instruments

	Outcomes	Instruments
Questionnaires	KOA-specific health-related quality of life	Knee Injury and Osteoarthritis Outcome Score (KOOS)
	Self-efficacy	Self-efficacy for managing Chronic Disease 6-Item Scale
	Self-management behaviors	Cognitive Symptom Management and Communication with Physicians
	Health-related quality of life	Euroquol five dimensions five level (EuroQol -EQ-5D-5L)
	Physical activity	International Physical Activity Questionnaire (IPAQ)
	Coping strategies	Brief COPE
Physical fitness tests	Aerobic Capacity	Six-Minute Walking Test (6 MWT)
	Functional lower-limb strength	Five-Repetition Sit to Stand Test (FRSTST)
	Mobility	Timed “Up-and-Go” test
	Flexibility upper limb	Back Scratch Test (BST)
	Flexibility lower limb	Chair Sit and Reach (CRS)
	Gait speed	6-Meter Test
	Balance	Standing Balance
	Hand strength	Hand grip test

#### Eligibility questionnaire

This questionnaire collects personal data (including name, phone contact, address, and email) and the inclusion and exclusion criteria for participation in the program. It will be available both online and on paper.

#### X-ray

Bilateral, anterior-posterior knee radiographs will be used to identify OA in the tibiofemoral joint, and sunrise views will be used to identify OA in the patellofemoral compartment. The severity of OA in the tibiofemoral and patellofemoral joint will be measured by a rheumatologist using the K-L grading scale [77].

#### Socio-demographic information

A questionnaire will be created by the researchers that poses demographic questions, including date of birth, race, sex, marital status, current occupation, occupation before retiring and education level. Body mass index (BMI) will also be calculated as weight (measured in kilograms) over height squared (height measured in meters).

#### Use of medicine

A list containing the names of all medications being used and their doses and indications will be requested from the patients before and after the intervention (baseline and post-intervention).

### Questionnaires

#### Knee Injury and Osteoarthritis Outcome Score (KOOS)

This questionnaire includes 5 dimensions to measure KOA-specific health-related quality of life (QOL), knee pain (Pain), other disease-specific symptoms (Other Symptoms), daily living activities (ADL), and sport/recreation functions (Sport/Rec). A score for each of the five dimensions is calculated as the sum of the items that are included, which is then converted to a 0–100 scale in which 0 represents extreme knee problems and 100 represents no knee problems. The KOOS has been validated for use in patients with knee injuries and patients with KOA and is a reliable and responsive self-administered instrument for short-term follow-ups [78].

#### Self-efficacy for managing chronic disease 6-item scale

This 6-item scale contains items taken from several self-efficacy scales that were developed for the Chronic Disease Self-Management study. This is a one to ten scale that includes six questions. The scale was tested on 605 subjects with chronic diseases [31]. The observed range of outcomes was 1-10 with a mean of 5.17, a standard deviation of 2.22, and an internal consistency reliability of 0.9.

#### Cognitive symptom management

This scale comprises six questions and has an observed range of 0–5. The scale was tested on 1129 subjects with chronic disease, and 51 of these subjects who underwent a test-retest protocol [79]. The mean result was 1.33 with a standard deviation of 0.91, an internal consistency reliability of 0.75 and a test-retest reliability of 0.83.

#### Communication with physicians

This questionnaire includes three questions. The scale was tested on 1130 subjects with chronic disease, and 51 of these subjects underwent a test-retest protocol [79]. The results showed an observed range of 0–5, a mean of 3.08, a standard deviation of 1.20, an internal consistency reliability of 0.73 and a test-retest reliability of 0.89.

#### Perception of health and quality of life (EuroQol - EQ-5D-5 L)

The EQ-5D-5L is a generic instrument for measuring health-related quality of life (HRQoL) that allows the generation of an index that represents a status value of the health of an individual. This scale is based on a classification system that describes health along the following five dimensions: mobility, personal care, usual activities, pain/discomfort, and anxiety/depression. Each of these dimensions has five levels of severity. This instrument employs psychometric techniques similar to those of the EQ-5D [80].

#### International Physical Activity Questionnaire (IPAQ)

The short form of the IPAQ was chosen because it is easy to apply. Its reliability has been verified in many countries and in different populations [81, 82].

#### Brief COPE

The first version of the COPE inventory by Carver, Scheier and Weintraub [83] was subsequently abbreviated by Carver [84]. The abridged version (brief COPE) contains only 28 items that are answered on a Likert 4-point scale (ranging from 1 = never use this strategy to 4 = I often use this strategy) and divided into the following 14 sub-scales (two items per scale): active coping, denial, substance use, emotional support, instrumental support, behavioral divestment, ventilation, revaluation, planning, mood, acceptance, religion, and self-blame. Data from a study of survivors of Hurricane Andrew indicate that the brief COPE scales have an adequate internal reliability [84].

### Physical fitness tests

#### Six-Minute Walk Test (6 MWT)

This test is a valid measure of aerobic capacity in older adults [85], and it has been used in studies of KOA [86, 87].

#### Five-Repetition Sit to Stand Test (FRSTST)

This measure is a widely used measure of functional strength. The ICC values for this test reveal good to high test-retest reliability for adults and subjects with osteoarthritis [86, 88, 89].

#### Timed “up-and-go”

This is a test of strength, agility and dynamic balance that incorporates multiple activity themes. The time (seconds) taken to rise from a chair, walk 3 m (9 ft, 10 inches), turn, walk back to the chair and then sit down wearing regular footwear (while using a walking aid if required) is assessed [90].

#### Chair Sit and Reach test (CSR)

The CSR test is a safe and socially acceptable alternative to traditional floor sit-and-reach tests and is a reasonably accurate and stable measure of hamstring flexibility [91]. The subjects are allowed three attempts for each limb, and the best of these scores is recorded to the nearest centimeter.

#### The Back Scratch Test (BST)

The BST is a measure of overall shoulder range of motion. This test involves measuring the distance, using a ruler, between (or overlap in) the middle fingers when they are placed behind the back [92]. After a practice trial, this test is assessed twice, alternating between both hands, and the best value is registered for each.

#### Six-meter test

This test measures linear walking ability, excluding acceleration and deceleration [93]. This variable is also used as a primary outcome in an algorithm for sarcopenia in older individuals [94].

#### Standing balance test

This test will be performed bilaterally. While near a wall, the subject crosses theirs arms over their chest, lifts the preferred leg off the floor without touching the other leg, and holds this position with their eyes open as long as possible. Contact between the legs, the support touching the ground, touching the wall and withdrawing the arms from the chest are considered errors. The evaluator stops recording the time upon the occurrence of any error. The participants will perform two repetitions of the test, and the best result will be recorded [95].

#### Hand Grip Test (HGT)

This test evaluates the maximal isometric force exerted by the muscles of the hand and forearm using a dynamometer. Although this study will not examine hand OA, this test has been used in the elderly as an indicator of sarcopenia and/or disability [96, 97]. Prior to the test, the grip dynamometer will be adjusted to the size of the hands of each subject. The subjects will stand with their arms along their bodies without contact with their trunk and with their elbows slightly bent at a 20° angle. Testing will first be conducted using the dominant hand and subsequently using the non-dominant hand. Strength will be evaluated during the expiratory phase to avoid the Valsalva maneuver. The best of three repetitions will be chosen for further analysis.

### Other measures

#### Patient’s Global Impression of Change (PGIC)

This scale is often used in clinical research, particularly in musculoskeletal studies [98]. The changes will be classified on dichotomous scales, and the classifications that will be used will include perceived change (5–7), an experience reflecting significant changes (1–4) and a lack of experience reflecting significant changes [98].

#### Visual Numeric Pain Scale (VNS)

This scale is used to self-report pain. It combines strong visual cues with an 11-point numeric rating scale. The VNS is highly correlated with the visual analogue scale (VAS, r = 0.85), is sensitive to changes in pain, and has been demonstrated to be a valid measure [71].

#### OMNI resistance exercise scale

This scale is a perceived exertion scale used with resistance exercise, and its high level of construct validity indicates that the OMNI-RES measures the same properties related to exertion as the Borg RPE scale [99] during resistance exercise [75].

### Data analysis

The data will be analyzed in a blinded manner. Descriptive statistics will be used to describe subject characteristics. The intervention and control groups will be examined for baseline comparability with respect to demographic and other factors. Kolmogorov-Smirnov tests will be used to test for normality. Univariate analyses of covariance (ANCOVA) will be conducted to compare changes between groups (i.e., the self-management and exercise group compared to the educational group) with adjustments for baseline values. The mean difference within groups will be calculated as Mom 1 (baseline) minus Mom 2 (after intervention program). The effect sizes will be verified using partial eta squared statistics. Repeated measures analyses using linear mixed models will be used to assess the constancy of any effects in the self-management and exercise group over time. Missing data will be assumed to be missing at random. All statistical analyses will be performed using IBM SPSS Statistics 22.0 and MedCalc Statistical Software (MedCalc Software, Mariakerke, Belgium), and significance will be established at a level of 5 %.

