### Aim and hypothesis

The aim of this study is to design and implement a PLE^2^NO program (in Portuguese: Free Program of Education and Exercise for Osteoarthritis) for elderly patients with KOA for a duration of three months. The PLE^2^NO is based on applying the principle of self-efficacy to manage the pathology. When patients gain confidence in taking control of their disease, they are more comfortable exercising and managing OA symptoms and consequently make better decisions about treatment. This allows them to increase their quality of life. To encourage participant’s adherence to and maintenance of the program and to contribute to pain control, all participants will receive a supplement containing CS and GlcN-S.

The following three hypotheses were therefore formulated. H1, self-reported KOA symptoms (i.e., pain and stiffness) and physical fitness will improve more in the self-management and exercise group than in the control group; H2, self-management skills and self-efficacy will improve more in the self-management and exercise group than in the control group; and H3, health-related quality of life, physical activity levels and coping strategies will improve more in the self-management and exercise group.

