## Methods and design

### Study design

The PLE^2^NO is a single-blinded, randomized controlled trial with a three-month duration and a six-month follow-up. The participants will be individually randomly assigned to one of two groups: (1) a self-management and exercise group or (2) an educational control group. Both groups will receive supplementation (CS and GlcN-S). Figure 1 provides a flowchart of the PLE^2^NO design. It will not be possible to blind the participants because of the nature of the intervention. However, the assessors will be blinded to group allocation.

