The randomization process will be performed on the baseline assessment day by the research team leader. The randomization sequence will be a 1:1 allocation to the two treatment arms.

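### The only stated analysis that reaches the 6-month visit is worded for the experimental arm alone, and no between-group contrast at 6 months is stated

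*Protocol article*

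**What the plan says.** The Study design section describes a "single-blinded, randomized controlled trial with a three-month duration and a six-month follow-up". Under Participants and procedures, "The randomization sequence will be a 1:1 allocation to the two treatment arms". The Assessments and procedures section says that all outcomes "will be assessed at baseline, post-intervention and a 6-month follow-up", with no restriction to one arm. The Discussion also lists three assessments.

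The hypotheses under Aim and hypothesis are comparative. H1, on symptoms and fitness, says that these "will improve more in the self-management and exercise group than in the control group". H2 says that "self-management skills and self-efficacy will improve more in the self-management and exercise group than in the control group". H3 is also worded as greater improvement in the experimental group.

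The Data analysis section names two inferential analyses of outcome:

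- A univariate ANCOVA that compares changes between the two groups, adjusted for baseline. The sentence names no visit. The next sentence defines the within-group mean difference as Mom 1 (baseline) minus Mom 2 (after the intervention). No Mom 3 is defined.
- A repeated-measures analysis in which "linear mixed models will be used to assess the constancy of any effects in the self-management and exercise group over time".

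No group-by-visit term and no between-group contrast at 6 months is stated.

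**The concern.** The effect of the programme is a difference between arms. Whether it lasts is a question about that difference at the later visit. The follow-up sentence instead asks whether something stays constant within the experimental arm.

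A course in one arm mixes the treatment effect with everything else that changes over time. Here that includes the natural course of the disease, regression to the mean after entry, and a supplement that both arms receive (Interventions section). Catch-up is also plausible: under Education control Group, controls receive a book with exercise information and three monthly sessions that cover exercise and self-management.

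The Discussion expects participants to continue on their own after the programme ends, so readers will want a durability result. As worded, the plan could report a maintained effect when no difference between arms remains, or a lost effect when the difference is intact. The control arm's 6-month measurements, which would settle the matter, have no stated inferential use.

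**Working it through.** **1. The plan's own figure.** The Sample size section gives a two-group ANCOVA with one covariate, effect size 0.35, 5% significance and 80% power, and reports 67 in total. Take 0.35 as Cohen's f and use a noncentral F with df1 = 1, df2 = N − 2 − 1 and noncentrality f² × N:

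- N = 66: noncentrality 0.1225 × 66 = 8.085, power 0.7995
- N = 67: noncentrality 0.1225 × 67 = 8.2075, power 0.806

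The smallest N that reaches 0.80 is 67, so the figure reproduces. The trial is sized on a comparison between two arms.

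**2. Visits and arms that the stated analyses reach.**

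- Baseline to post-intervention: ANCOVA, both arms.
- 6-month visit, self-management and exercise group: the mixed model.
- 6-month visit, education group: measured, but no analysis is stated.

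**3. What each analysis estimates.** Let S1 and S2 be the mean change from baseline in the experimental arm at post-intervention and at 6 months, and C1 and C2 the same in the control arm. Change is taken here as later minus baseline, so that a higher KOOS score counts as improvement.

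- Treatment effect at post-intervention: D1 = S1 − C1. The ANCOVA addresses this.
- Treatment effect at 6 months: D2 = S2 − C2.
- Change in the effect: D2 − D1 = (S2 − S1) − (C2 − C1).

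A model of the experimental arm estimates only S2 − S1. It equals the change in the treatment effect only if C2 − C1 = 0, that is, if the control arm stays still. The randomised control arm is there so that this need not be assumed.

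**4. Two cases in which the one-arm reading misleads.**

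- Catch-up: S2 − S1 = 0 and C2 − C1 = D1. Then D2 = D1 + 0 − D1 = 0. The experimental arm is perfectly constant and no benefit over control remains.
- Common drift: S2 − S1 = C2 − C1 = −x. Then D2 = D1 − x + x = D1. The experimental arm declines, yet the benefit over control is intact.

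**5. Can the trial support the 6-month contrast?** The Sample size section plans 80 recruits and 20% dropout, so 80 × 0.80 = 64 completers. With the formula of step 1 and the same f of 0.35, power is 0.787 with 64, 0.806 with 67 and 0.871 with 80. This assumes that f is the same at 6 months and that the 20% covers loss up to that visit. The document states neither. Under those assumptions the contrast has about the power for which the trial was planned.

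**The case against.** The strongest reply is that the wording is loose rather than wrong. The phrase about effects in the experimental group may mean effects relative to control, already estimated by the ANCOVA and then followed over time. The sentence does not say that the model is fitted to one arm's data. The ANCOVA sentence names no visit, and the Mom 1 minus Mom 2 sentence defines a within-group difference, so an ANCOVA of the 6-month change is unstated rather than excluded. An article may also leave model terms to a fuller document.

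Part of this stands. A reader might infer that the control arm's 6-month data are never used. The text supports only that no inferential use is stated. The reply does not remove the point, because the article does more than leave out detail: it names the follow-up method and ties it to one arm, and the only change it defines ends at post-intervention. An analysis plan that followed this wording would carry the problem forward. If effects against control were meant, one sentence would say so.

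A reader might also infer a conflict with the statement that "The data will be analyzed in a blinded manner", since one arm is named in the model. That does not hold. The arms can be coded and the model run for each code, under the present wording as well as under a two-arm model.

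**Conclusion.** The point holds as a should-fix matter. The follow-up analysis is worded around one arm, and no 6-month between-group contrast is stated, although both arms are measured then and the hypotheses are comparative. This rests on the ordinary reading of the mixed-model sentence. On the looser reading, the text still needs correcting for clarity.

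The reach is limited to durability. The aim concerns a three-month programme, no hypothesis names the 6-month visit, and the baseline-adjusted comparison at post-intervention is planned for both arms. A reader might infer that the trial's main randomised comparison is lost. The documents do not support that.

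No error rate is attached. A reader might calculate how often a one-arm test would wrongly report constancy. That needs a rule that a non-significant within-arm change counts as constant, plus correlations between visits, and the protocol gives neither. The argument in steps 3 and 4 of the working needs no such figures.

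**What to change.** Replace the mixed-model sentence with one to this effect: a linear mixed model will be fitted to both randomised arms over all scheduled visits, with fixed effects for group, visit and group-by-visit and with adjustment for the baseline value. The adjusted between-group difference will be reported with its 95% confidence interval at post-intervention and at 6 months. Durability will be judged by the 6-month difference and by the change in the between-group difference from post-intervention to 6 months.

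The course within the experimental arm can stay as a description.

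The cost is one sentence. The data are already to be collected in both arms, and the method and software are already planned. No change to sample size, visits or the post-intervention ANCOVA is needed.

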## Discussion

It is essential to identify the best approach to treating patients with KOA. Such an approach should consider the individuals’ quality of life, international recommendations for treatment and the availability of health services. Therefore, the combined use of self-management, exercise and supplements (glucosamine and chondroitin sulfate) appears to be a feasible and effective option for treating elderly patients with KOA.

There are several strengths to the design and implementation of this study protocol. First and foremost, this program combines the recommendations of international organizations (OARSI, EULAR and ACR) with a combination of exercise and educational (self-management) programs. The study design is extremely current, ambitious and grounded.

Second, the program will be administered in close proximity to the patients. To achieve this goal, the program will take place at four different locations: two senior universities, one church, and one community center. This is necessary because when we consider the age and pathological conditions that we expect to find in the study patients, locomotion may be a barrier. Therefore, if a patient will not be able attend for financial reasons, a van from a church or a team member’s car will provide transportation services. These efforts will minimize the problem of access to the classes.

Third, the methodology of the program, in terms of both self-management and exercise, has been planned in extreme detail using simple resources, including paper roles for the self-management component and elastic bands, ankle weights and chairs for the exercise components. Thus, the program can be feasibly disseminated (e.g., it uses minimal, low-cost equipment and has few storage requirements). The exercise program will be administered by highly qualified exercise instructors, two of whom have master’s degrees in Sport Science and the Science of Physiotherapy, and one other instructor who is an Exercise and Health master’s student from the Faculty of Human Kinetics. All of these instructors specialize in exercise, health and fitness group skills. Furthermore, a certified leader of the Chronic Disease Self-Management Program (CDSMP) at Stanford University will administer the self-management program.

The program will also have a self-efficacy component for exercise, with a goal that following the end of the program, the patients will continue doing exercises, and they will receive support in this endeavor, including access to the materials that were used in the program, a chart with a description of all of the exercises that they performed in class and a brief explanation about how these exercises should be performed.

With the exception of the knee radiographs for the OA diagnoses, all measurements will be obtained at the same place at baseline immediately after the end of the program and at the 6-month follow-up. Therefore, to support the project, the staff team includes one secretary who is responsible for the administrative work and four health professionals who will conduct the tests and questionnaires. To avoid inter-rater error, the same health professionals will lead the applications of the three assessments, i.e., the baseline, post-intervention and follow-up assessments.

Participant adherence to the exercise program is one of the main challenges, mainly because the participants are elderly and susceptible to other health problems. Therefore, motivational cues, intragroup social interactions, frequent telephone calls and the quality of the professors are the main strategies that have been selected to prevent the occurrence of dropouts.

One possible constraint to the success of the program is the extensive exclusion criteria, but these criteria are required to maintain the quality of the study. In this study, all adverse events will be documented and reported from screening until study completion.

Our study is based on the premise that elderly patients with KOA need an appropriate treatment regimen that is accessible and achievable, given their condition. Therefore, the study treatment regimen was designed to develop their self-efficacy to manage their own condition. The concepts of autonomy, self-management and self-efficacy are therefore essential. Moreover, once the program ends, the participants are expected to continue the treatment using self-management skills and by performing the exercises on their own, which should consequently assist them in coping better with pain and KOA symptoms.

The findings of this study will contribute to clinical trial reference data for elderly individuals with KOA by adding information regarding the effectiveness of combining a self-management strategy with an exercise program.

The format of the sessions, the study duration and the weekly frequency of the program are organized in a manner that ensures that this proposal is executable not only for this project but also for future implementations by communities.

